# Efficacy and Safety of Electroacupuncture Through Nerve Stimulation in Patients With Anxiety Disorders: Protocol for a Randomized, Assessor-Blind, Three-Arm, Parallel-Group Clinical Trial

**DOI:** 10.2196/68166

**Published:** 2025-07-21

**Keywords:** anxiety disorders, electroacupuncture, nerve stimulation, vagus nerve, median nerve

## Abstract

**Background:**

Anxiety disorders are among the most common mental health disorders, affecting a significant portion of the population. However, conventional treatments, such as pharmacotherapy and psychotherapy, often have limited effectiveness and may lead to undesirable side effects. Consequently, there is a growing demand for new alternative treatments for anxiety disorders. Recent studies suggest that electroacupuncture may demonstrate therapeutic effects in managing anxiety by mediating nerve stimulation.

**Objective:**

This study is designed to assess the efficacy and safety of electroacupuncture in treating anxiety disorders through nerve stimulation. Specifically, it will involve stimulating the median nerve at the PC6 acupoint (Neiguan) and the vagus nerve at the TF4 acupoint (Shenmen of ear acupuncture).

**Methods:**

This study is a randomized, assessor-blind, three-arm, parallel-group clinical trial comprising the PC6 electroacupuncture group, TF4 electroacupuncture group, and a control group. Participants will include patients diagnosed with social anxiety disorder, panic disorder, agoraphobia, and generalized anxiety disorder. Eligible participants will be randomly assigned to one of the 3 groups, with each group containing 20 individuals. The electroacupuncture groups will receive treatments at the designated acupoints twice weekly for 8 weeks, totaling 16 sessions. The control group will receive usual care without any treatment interventions through the end of the study period. The primary outcome is the comparison of Hamilton Anxiety Rating Scale scores between the treatment groups and the control group. Secondary outcomes include scores on the Hamilton Anxiety Rating Scale, Beck Anxiety Inventory, Beck Depression Inventory-II, Patient Health Questionnaire-15, World Health Organization Quality of Life Assessment Instrument abbreviated version, Penn State Worry Questionnaire, Panic Disorder Severity Scale, and Leibowitz Social Anxiety Scale. Safety evaluation variables include the frequency of adverse events, vital signs, and suicide risk assessment. Exploratory variables include performance on the Emotional Reactivity Test, empathy quotient, and heart rate variability.

**Results:**

The first participant was enrolled on December 15, 2022. As of October 2024, a total of 60 participants have been fully registered, and the intervention is currently in progress. We expect the completion of this trial to occur within the year 2025.

**Conclusions:**

In this study, we will evaluate the safety and efficacy of electroacupuncture for anxiety disorders. By elucidating the therapeutic mechanisms of electroacupuncture through nerve stimulation, this study will provide clinical evidence to support the development of potential interventions for patients with anxiety disorders.

**Trial Registration:**

Clinical Research Information Service of the Republic of Korea KCT0008378; https://cris.nih.go.kr/cris/search/detailSearch.do/24503

**International Registered Report Identifier (IRRID):**

DERR1-10.2196/68166

## Introduction

Anxiety disorders are defined as mental health conditions that are characterized by a set of symptoms, including excessive fear, anxiety, and related behavioral disturbances [1]. Anxiety disorders represent a significant proportion of mental health conditions, affecting an estimated 301 million people worldwide as of 2019 [2]. The prevalence of anxiety disorders is increasing due to factors such as an aging population, urbanization, and socioeconomic development [3]. These disorders not only result in substantial socioeconomic consequences but also pose a threat to the ongoing growth and productivity of societies [4]. Therefore, the treatment and management of anxiety disorders are becoming increasingly important.

Treatment for anxiety disorders has been found to be effective with pharmacotherapy such as antidepressants and benzodiazepines [5], and psychotherapies like cognitive behavioral therapy and eye movement desensitization and reprocessing are also used [6,7]. However, pharmacotherapy raises concern due to side effects and resistance [8,9], and is often met with negative perceptions by patients regarding psychiatric medications [10]. In addition, although psychotherapy is generally effective, it is neither always cost-effective nor consistently successful [11,12]. Thus, there is a need for treatments that are both cost-effective and associated with fewer adverse effects.

Recent studies suggest that acupuncture and electroacupuncture are effective treatments for anxiety disorders with fewer adverse effects compared to conventional pharmacotherapy [13,14]. Consequently, both acupuncture and electroacupuncture are being recommended as alternative methods for the chronic management and long-term treatment of anxiety disorders [15].

This study aims to assess the efficacy and safety of electroacupuncture treatment for anxiety disorders, with a particular focus on treatments at acupoints PC6 (Neiguan) and TF4 (Shenmen of ear acupuncture), compared with a control group.

## Methods

Study Design

This study is designed as a randomized, 3-arm assessor-blinded, parallel-group clinical trial, which will be conducted at the Daejeon Korean Medicine Hospital of Daejeon University, Republic of Korea. It aims to evaluate the efficacy and safety of 2 distinct electroacupuncture interventions in the treatment of anxiety disorders, in comparison to usual care. The interventions specifically target to stimulate the median nerve via acupoint PC6 and the vagus nerve via acupoint TF4 (Figures 1 and 2) [16,17]. The control group, constituting usual care, will not receive any treatment.

**Figure 1 figure1:**
[figure not shown]
Acupoint PC6. Adapted from Li et al [16], under the Creative Commons Attribution 4.0 International License (CC BY 4.0).

**Figure 2 figure2:**
[figure not shown]
Acupoint TF4. Adapted from Qu et al [17], under the Creative Commons Attribution 4.0 International License (CC BY 4.0).

To ensure the rigor and validity of our findings, this study protocol (version 1.4, June 2023) adheres to the SPIRIT (Standard Protocol Items: Recommendations for Interventional Trials) guidelines.

Study Procedure

During the initial screening visit, potential participants will receive a comprehensive explanation of the study’s purpose, procedures, risks, and benefits and will be asked to provide written consent. Those who voluntarily consent and meet the inclusion and exclusion criteria—as determined through demographic information surveys, medical and medication history reviews, vital signs measurements (blood pressure, pulse, and temperature), laboratory tests, pregnancy tests, the Structured Clinical Interview for *DSM-5* (*Diagnostic and Statistical Manual of Mental Disorders* [Fifth Edition]; SCID-5) [18], and the Columbia Suicide Severity Rating Scale (C-SSRS) [19]—may be enrolled in this study. The SCID-5 will be used to diagnose subtypes of anxiety disorders, including social anxiety disorder, panic disorder, agoraphobia, generalized anxiety disorder, and other specified anxiety disorders. Participants who do not meet the diagnostic criteria for an anxiety disorder as per the SCID-5 will be excluded from the study. The C-SSRS will be used to assess the risk of suicide; participants scoring 4 or above, indicating a high risk of suicide, will also be excluded from study selection.

Following registration, participants will be randomly assigned to one of the three groups: the electroacupuncture-vagus nerve stimulation (EA-VNS) group, the electroacupuncture-median nerve stimulation (EA-MNS) group, or the usual care group. Participants in the treatment groups will undergo electroacupuncture sessions twice weekly for a total of 16 sessions over 8 weeks. Conversely, the usual care group will not receive any interventions during this period.

The evaluation of the treatment group is scheduled to occur at the initial, eighth, and final visits. For the control group, assessments will be conducted in the first, fourth, and eighth weeks. During the initial and final assessments for the treatment group, and the first and eighth weeks for the control group, the following instruments will be administered: Hamilton Anxiety Rating Scale (HAM-A) [20], Beck Anxiety Inventory (BAI) [21], Beck Depression Inventory-II (BDI-II) [22], Patient Health Questionnaire-15 (PHQ-15) [23], World Health Organization Quality of Life Assessment Instrument abbreviated version (WHOQOL-BREF) [24], Leibowitz Social Anxiety Scale-Self Report (LSAS-SR) [25], The Panic Disorder Severity Scale (PDSS) [26], and Penn State Worry Questionnaire (PSWQ) [27]. LSAS-SR will be conducted only for patients with social anxiety disorder, PDSS only for those with panic disorder or agoraphobia, and PSWQ only for those with generalized anxiety disorder. A midpoint evaluation using the HAM-A and BAI will be conducted during the eighth visit for the treatment group or in the fourth week for the control group. The detailed schedules are described in Table 1 and the study flow is presented in Figure 3.

**Table 1 table1:** Timeline of the trial.

Period				Screening (week –1)		Treatment									
						Baseline (week 0)	Midterm						Final (week 8)		
							Weeks 1-4		Week 4		Week 5-8				
Visit						Visit 1^a^	Visit 2-7^b,c^		Visit 8		Visit 9-15		Visit 16		
Consent				✓											
Demographic information				✓											
Medical history				✓		✓	✓		✓		✓		✓		
Physical examination				✓											
Vital signs				✓		✓	✓		✓		✓		✓		
Body weight and height				✓									✓		
Laboratory test^d^				✓											
Pregnancy test^e^				✓											
SCID-5^f^				✓											
C-SSRS^g^				✓									✓		
Inclusion and exclusion criteria				✓											
Randomization						✓									
	Item														
		HAM-A^h^, BAI^i^				✓			✓				✓		
		PHQ-15^j^, BDI-II^k^				✓									
		WHOQOL-BREF^l^				✓							✓		
		PSWQ^m^, PDSS^n^, LSAS-SR^o^				✓							✓		
		EQ^p^, PSS^q^				✓							✓		
Emotional reactivity test						✓							✓		
Check concomitant drugs						✓	✓		✓		✓		✓		
Check adverse effects						✓	✓		✓		✓		✓		
EA-MNS^r^, EA-VNS^s^						✓	✓		✓		✓		✓		
HRV^t^						✓			✓				✓		
Education of visit schedule				✓		✓	✓		✓		✓				

^a^Visit 1 is scheduled to occur within 10 days of screening.

^b^Visits 2-7 are implemented 4 times within 2 weeks + 2 days from visit 1. Similarly, visits 9- 15 are implemented 4 times within 2 weeks + 2 days after visit 8. Electroacupuncture treatments are typically scheduled twice a week, but once to three visits per week are permitted.

^c^Only the experimental group follows this schedule.

^d^Lab test items are as follows: complete blood cell count (red blood cell, white blood cell, hemoglobin, hematocrit, platelet, erythrocyte sedimentation rate, white blood cell differential count), blood chemistry test (aspartate aminotransferase, alanine aminotransferase, blood urea nitrogen, creatinine, and hemoglobin A_1c_), thyroid function test (triiodothyronine, free thyroxine, and thyroid stimulating hormone), pregnancy test (urine human chorionic gonadotropin, applicable only to fertile women).

^e^A pregnancy test is only performed for fertile women who have had a menstrual period within the last year.

^f^SCID-5: Structured Clinical Interview for DSM-5 (Diagnostic and Statistical Manual of Mental Disorders [Fifth Edition]).

^g^C-SSRS: Columbia Suicide Severity Rating Scale.

^h^HAM-A: Hamilton Anxiety Rating Scale.

^i^BAI: Beck Anxiety Inventory.

^j^PHQ-15: Patient Health Questionnaire-15.

^k^BDI-II: Beck Depression Inventory-II.

^l^WHOQOL-BREF: World Health Organization Quality of Life Assessment Instrument abbreviated version.

^m^PSWQ: Penn State Worry Questionnaire. This has been used for generalized anxiety disorder and other anxiety disorders.

^n^PDSS: Panic Disorder Severity Scale.

^o^LSAS-SR: Leibowitz Social Anxiety Scale-Self Report. This has been for social anxiety disorder.

^p^EQ: Empathy Quotient.

^q^PSS: Perceived Stress Scale.

^r^EA-MNS: electroacupuncture-median nerve stimulation. This will be conducted according to each group.

^s^EA-VNS: electroacupuncture-vagus nerve stimulation. This will be conducted according to each group.

^t^HRV: heart rate variability.

**Figure 3 figure3:**
[figure not shown]
Flowchart of study procedure. EA-MNS: electroacupuncture-median nerve stimulation; EA-VNS: electroacupuncture-vagus nerve stimulation;.

### Study Populations

To ensure the safety of participants and the integrity of study outcomes, specific inclusion and exclusion criteria were applied. These criteria were designed to select individuals with appropriate clinical characteristics for the study intervention while minimizing potential risks and confounding variables. Eligible participants were required to meet all inclusion criteria and none of the exclusion criteria listed in Textbox 1.

Inclusion and exclusion criteria.Inclusion criteria:(1) Aged 19-70 years, as individuals aged 19 years and older are legally permitted to provide autonomous consent to participate in clinical research in Korea.(2) Diagnosed with an anxiety disorder including social anxiety disorder, panic disorder, agoraphobia, generalized anxiety disorder, other specified anxiety disorders, and unspecified anxiety disorder as assessed through the Structured Clinical Interview for *DSM-5* (*Diagnostic and Statistical Manual of Mental Disorders* [Fifth Edition]; SCID-5).(3) Voluntarily decided to participate in this study and signed the written consent form.(4) Able to complete electroacupuncture-neural stimulation treatments over 8 weeks.Exclusion criteria:(1) At high risk of suicide as assessed by the Columbia-Suicide Severity Rating Scale with a score of 4 or more.(2) With a history of schizophrenia or bipolar disorder.(3) Diagnosed with separation anxiety disorder, selective mutism, substance-induced anxiety disorder, anxiety disorder due to medication, or anxiety disorder due to other medical conditions.(4) Received acupuncture treatment within the last 4 weeks.(5) With a history of alcohol or other substance use disorders within the last 8 weeks.(6) With a history of cerebrovascular disease, brain tumor, or traumatic brain injury.(7) With a history of neurological or systemic disease that may affect the central nervous system.(8) In medical conditions requiring inpatient treatment.(9) Usage of a pacemaker.(10) With contraindications to acupuncture treatment (eg, acupuncture-associated vasovagal response or tissue damage due to acupuncture).(11) Taken medication or participated in another clinical trial within the last month.(12) Pregnant or lactating women, or those not using medically acceptable methods of contraception during the study period.(13) Deemed inappropriate for enrollment due to other reasons as determined by the investigators.

### Interventions

In this study, electroacupuncture treatments will be administered by qualified Korean medical doctors with at least 1 year of clinical experience. Participants assigned to the electroacupuncture treatment groups will receive treatments twice a week, with a total of 16 sessions over an 8-week period. Each session will last 20 minutes. For the EA-MNS group, the needle will be inserted at PC6, while for the EA-VNS group, the needle will be inserted at TF4. The selection of these intervention sites is based on previous studies showing that stimulation of the median nerve or PC6 acupoint and the vegus nerve or TF4 acupoint is effective for alleviating anxiety symptoms [15,28,29].

The needles will be stimulated using an electroacupuncture stimulator (model STN-110, Streatek Co). For the electroacupuncture-median nerve stimulating group, needles will be inserted at PC6 and at a nonacupoint approximately 0.5 cm proximal to PC6 on the right arm. Subsequently, the hook-shaped or magnetic output terminal of the electroacupuncture stimulator will be attached to administer electrical stimulation. The electrical stimulation for EA-MNS will be conducted at 12 Hz for 20 minutes. For the electroacupuncture-vagus nerve stimulating group, needles will be inserted at TF4 and at a nonacupoint surrounding 0.7 to 1.0 cm away from TF4 on the right ear. The method of attaching the electroacupuncture stimulator is the same as for the EA-MNS group. The electrical stimulation for EA-VNS will be conducted at 100 Hz for 20 minutes. In both groups, the intensity of the electrical stimulation (in mA) will be set to a level that the participant reports as a 4 to 5 on a scale from 0 to 10. The Standards for Reporting Interventions in Clinical Trials of Acupuncture (STRICTA) for acupuncture treatment is described in Multimedia Appendix 1.

### Criteria for Concomitant Drugs

#### Permissible Drugs

Drugs that have been taken consistently at a stable dose for at least 4 weeks before study participation and are not expected to interfere with the interpretation of the clinical trial results may be permitted at the discretion of the researcher. In addition, drugs intended for the transient treatment of other conditions can be coadministered after consultation with the researcher. Comprehensive details of all concomitant drugs—including the name of the drug, purpose of administration, dosage, and duration—will be documented in the case report form.

#### Prohibited Drugs

During the trial period, the administration of drugs that may influence anxiety symptoms is prohibited, including systemic steroids, antipsychotics, antidepressants, benzodiazepines, and sleeping pills. However, if antidepressants, benzodiazepines, and sleeping pills have been administered at a stable dose for at least 2 weeks before screening, their continuous use may be permitted.

### Efficacy Variables

The primary, secondary outcome measures, and research hypotheses are summarized in Textbox 2.

Efficacy variables.
**Primary Outcome**
The primary outcome will be assessed by analyzing changes in the Hamilton Anxiety Rating Scale (HAM-A) scores from baseline to week 8 in two separate comparisons:Between the electroacupuncture-median nerve stimulation (EA-MNS) group and the Usual Care group.Between the electroacupuncture-vagus nerve stimulation (EA-VNS) group and the Usual Care group.Research HypothesisHypothesis 1 [H0 : μ1 = μ2, H1 : μ1 ≠ μ2]μ1: Changes in HAM-A score from baseline to week 8 in the EA-MNS groupμ2: Changes in HAM-A score from baseline to week 8 in the Usual Care groupHypothesis 2 [H0 : μ3 = μ2, H1 : μ3 ≠ μ2]μ2: Changes in HAM-A score from baseline to week 8 in the Usual Care groupμ3: Changes in HAM-A score from baseline to week 8 in the EA-VNS group
**Secondary Outcomes**
The secondary outcomes will be assessed as follows:Changes in HAM-A scores from baseline to week 8 between the EA-MNS group and the EA-VNS group.Evaluation of rates of loss of diagnosis and complete remission of anxiety disorder, as measured by HAM-A scores, from baseline to week 8 between the EA-MNS group and the Usual Care group.Evaluation of rates of loss of diagnosis and complete remission of anxiety disorder, as measured by HAM-A scores, from baseline to week 8 between the EA-VNS group and the Usual Care group.Evaluation of rates of loss of diagnosis and complete remission of anxiety disorder, as measured by HAM-A scores, from baseline to week 8 between the EA-MNS group and the EA-VNS group.Changes in Beck Anxiety Inventory (BAI), Beck Depression Inventory-II (BDI-II), Patient Health Questionnaire-15 (PHQ-15), World Health Organization Quality of Life Assessment Instrument abbreviated version (WHOQOL-BREF), Penn State Worry Questionnaire (PSWQ), Panic Disorder Severity Scale (PDSS), and Leibowitz Social Anxiety Scale-Self Report (LSAS-SR) scores from baseline to week 8 between the EA-MNS group and the Usual Care group.Changes in BAI, BDI-II, PHQ-15, WHOQOL-BREF, PSWQ, PDSS, and LSAS-SR scores from baseline to week 8 between the EA-VNS group and the Usual Care group.Changes in BAI, BDI-II, PHQ-15, WHOQOL-BREF, PSWQ, PDSS, and LSAS-SR scores from baseline to week 8 between the EA-MNS group and the EA-VNS group.

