#### Secondary Outcomes

The analysis of secondary outcome variables will adhere to the same methodology used for the primary outcomes. Changes in continuous variables from baseline to week 8 in BDI-II, BAI, PHQ-15, WHOQOL-BREF, PSWQ, PDSS, and LSAS-SR will be assessed using the same analytical approach, with a significance level set at 5%. To evaluate the differences in measurements before and after the intervention within each group, the Student Paired *t* test or Wilcoxon signed rank test will be used for both primary and secondary outcomes. Additionally, to examine the trend changes over time between the EA-MNS and EA-VNS groups, Repeated Measures ANOVA will be conducted. This analysis will include testing the interaction between the groups and visits to ascertain how differences evolve over time. If the interaction is found to be significant, post hoc tests will be implemented to identify significant differences between the groups at specific time points based on baseline measurements. Furthermore, the binary variables such as loss of diagnosis and complete remission of anxiety disorder, as assessed by HAM-A, will be compared between groups using logistic regression, which will provide odds ratios and 95% CI.

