### Statistical Methods to Handle Missing Data

When using the MMRM for variable analysis, no separate imputation for missing values will be conducted. Conversely, in cases where ANCOVA is used, missing values will be imputed using the Multiple Imputation method.

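### Loss of diagnosis is scored from HAM-A, but diagnosis is made by SCID-5 at screening only, so no week-8 data can show that a diagnosis was lost

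*Protocol article*

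**What the plan says.** **How a diagnosis is made.** Under Study Procedure, "The SCID-5 will be used to diagnose subtypes of anxiety disorders", and "Participants who do not meet the diagnostic criteria for an anxiety disorder as per the SCID-5 will be excluded from the study". The inclusion criteria (Textbox 1) rest on the same interview and reach as far as "other specified anxiety disorders, and unspecified anxiety disorder as assessed through the Structured Clinical Interview for" DSM-5. No inclusion or exclusion criterion names a HAM-A score.

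**When each instrument is used.** Table 1 ticks SCID-5 once, under screening (week –1). HAM-A is ticked at baseline, week 4 and week 8, and not at screening. Study Procedure also lists what is given at the initial and final assessments of the treatment groups, and for controls says that in "the first and eighth weeks for the control group, the following instruments will be administered". The list is HAM-A, BAI, BDI-II, PHQ-15, WHOQOL-BREF, LSAS-SR, PDSS and PSWQ. SCID-5 is not on it.

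**How the endpoint is defined.** Textbox 2 (Secondary Outcomes) gives "Evaluation of rates of loss of diagnosis and complete remission of anxiety disorder, as measured by HAM-A scores, from baseline to week 8" for EA-MNS against usual care, EA-VNS against usual care, and EA-MNS against EA-VNS. The statistical section on secondary outcomes repeats the source: "binary variables such as loss of diagnosis and complete remission of anxiety disorder, as assessed by HAM-A, will be compared between groups using logistic regression", with odds ratios and 95% CIs.

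**The concern.** Two instruments do different jobs here. SCID-5 decides whether a participant has an anxiety disorder and which one. HAM-A grades how severe the anxiety is. An endpoint called *loss of diagnosis* says that someone who met diagnostic criteria at entry no longer meets them. That needs the diagnostic instrument at both ends, and the plan has it at one end only.

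The label matters because readers will take it literally. A between-group difference in *loss of diagnosis* reads as recovery from the disorder, a stronger claim than a difference in symptom severity. Three comparisons are planned under that name.

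The companion endpoint, complete remission, has a lesser weakness. Entry needs a SCID-5 diagnosis but no severity floor, other specified and unspecified anxiety disorder are eligible, and stable antidepressants, benzodiazepines or sleeping pills may be continued. Some participants may therefore start with a low HAM-A. Under an absolute week-8 cut-off they could be counted as remitted although nothing changed.

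**Working it through.** **Step 1: Is there a week-8 source for loss of diagnosis?** The article gives no rate, cut-off or power for this endpoint, so there is no figure to reproduce. The check is to set the sections side by side.

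| Question | Where | Answer |
|---|---|---|
| What establishes the diagnosis? | Study Procedure; Textbox 1 | SCID-5 |
| When is SCID-5 done? | Table 1 | Screening only |
| Is SCID-5 among the final assessments? | Study Procedure | No |
| What scores loss of diagnosis at week 8? | Textbox 2; statistical section on secondary outcomes | HAM-A |
| Does HAM-A take part in eligibility? | Textbox 1; Table 1 | No; first taken at baseline |

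The wording can be read in two ways. If HAM-A scores both endpoints, loss of diagnosis is decided by an instrument that never established the diagnosis. If HAM-A is meant for remission only, loss of diagnosis has no week-8 data source. Neither reading gives a measured loss of a SCID-5 diagnosis.

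**Step 2: How many could meet a remission cut-off at baseline?** The documents give neither a baseline HAM-A distribution nor a cut-off. Assumptions: normal baseline scores, mean 15 to 20, SD 6 to 7, cut-off 7 (score of 7 or less, continuity-corrected to 7.5). The share is q = Φ((7.5 − mean)/SD).

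| Mean | SD | z | q | Expected of 20 |
|---|---|---|---|---|
| 20 | 6 | −2.08 | 1.9% | 0.4 |
| 20 | 7 | −1.79 | 3.7% | 0.7 |
| 15 | 6 | −1.25 | 10.6% | 2.1 |
| 15 | 7 | −1.07 | 14.2% | 2.8 |

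The range is about 2% to 14%, or roughly 0 to 3 of 20 per arm. It depends heavily on the assumptions: means of 14 to 22, SDs of 5 to 9 and cut-offs of 7 or 10 give 0.2% to 35%.

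**Step 3: What would that do to the comparison?** Suppose true remission among those above the cut-off at baseline is 10% in control and 40% in treatment (both assumed), and the share q stays low in both arms. The observed rate in each arm is q + (1 − q)p. Power is for 20 per arm, two-sided 5%.

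| q | Control | Treatment | Odds ratio | Power |
|---|---|---|---|---|
| 0 | 10.0% | 40.0% | 6.0 | 60% |
| 2% | 11.8% | 41.2% | 5.2 | 56% |
| 5% | 14.5% | 43.0% | 4.4 | 51% |
| 10% | 19.0% | 46.0% | 3.6 | 44% |
| 14% | 22.6% | 48.4% | 3.2 | 40% |

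Both rates rise and the odds ratio moves toward 1. At q = 5%, participants who never changed make up 0.05/0.145 = 34% of control remitters.

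**The case against.** The strongest reply is that the article states its measure openly: it says HAM-A is the source, so an attentive reader is not misled. It adds that this is a label on a secondary endpoint in a trial whose primary analysis is HAM-A change. The second part stands and limits the weight of the point. The first does not remove it: stating the source does not make a severity score a diagnosis.

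A reader might infer several stronger points that the article does not support.

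- *Low scorers will be counted as remitted.* The remission rule is not shown. Measuring from baseline to week 8 is compatible with a required reduction or a required starting score, and either would prevent this. The missing cut-off may sit in the full protocol or SAP and is not a finding.
- *The logistic model leaves out baseline HAM-A.* The article does not say so. Its secondary analyses are to follow the primary methodology, and baseline characteristics that differ between groups may enter as covariates. It is silent on covariates for this model.
- *The binary endpoints will be analysed on complete cases.* The missing-data section covers MMRM and ANCOVA ("When using the MMRM for variable analysis, no separate imputation for missing values will be conducted") and is silent on binary outcomes, a detail commonly left to the SAP.
- *A zero cell is likely, so the odds ratio will be infinite.* With an assumed control remission of 5% to 10%, the chance of no remitter among 20 controls is 0.95^20 = 36% to 0.90^20 = 12%. That is a risk, not the likely outcome. Low starters counted as remitted would add control events and lower it.
- *The endpoint favours electroacupuncture.* Randomisation makes low starters equally likely in each arm. The expected effect is dilution, although chance imbalance is possible with 20 per arm.

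**Conclusion.** The contradiction over *loss of diagnosis* holds and needs no assumption. The trial diagnoses by SCID-5, does not repeat it, and names a HAM-A result after it. No later analysis document can supply the missing interview, since the Results section says data collection ended on November 22, 2024. The three comparisons can be reported as differences in HAM-A severity, not as diagnostic recovery.

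The weakness in the remission endpoint is conditional on an absolute week-8 cut-off. Given that, and the assumed baseline values, about 2% to 14% of each arm could count as remitted without change. In the worked example the odds ratio falls from 6.0 to between 5.2 and 3.2. This costs sensitivity and does not create a false benefit in expectation. The change is worth making before results are reported. The primary outcome is unaffected.

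**What to change.** 1. Drop *loss of diagnosis* from the secondary outcomes, or rename it as a HAM-A severity category, in Textbox 2 and in the statistical section on secondary outcomes. Do not describe the result as diagnostic recovery.
2. Keep one HAM-A remission endpoint.
3. State that its logistic regression includes baseline HAM-A as a covariate, whether or not the groups differ at baseline, so that each participant's starting level is taken into account.

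The cost is one endpoint label and a few lines of wording. No new data are needed, because HAM-A is already scheduled at baseline and week 8. The article says analysis is under way, so the change should be dated and, if possible, made before the between-group results for these endpoints are seen.
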